## Abstract

**Background:**

With an aging population, knee arthroplasty is increasingly common; however, chronic postsurgical pain (CPSP) affects up to 30% of patients. This study aims to evaluate the efficacy of 5% lidocaine-medicated plaster (LP5) in preventing CPSP among patients undergoing knee arthroplasty.

**Methods:**

This is a dual-center, randomized, double-blind, placebo-controlled trial involving 128 adult patients scheduled for knee arthroplasty. Participants will be randomly assigned, stratified by center, to either the LP5 group or the placebo group (n = 64 per group). The LP5 or placebo group will apply the patch 1 day before surgery and on postoperative days 1–3, with multimodal analgesia administered postoperatively. Multimodal analgesia will include intraoperative flurbiprofen axetil and postoperative patient-controlled sufentanil. The primary outcome is the pain subscale of the Western Ontario and McMaster Universities Osteoarthritis Index (WOMAC) at 3 months postoperatively. Secondary outcomes will include WOMAC stiffness, function, and total scales; Leeds Assessment of Neuropathic Symptoms and Signs (LANSS) Pain Scale; 36-Item Short Form Health Survey (SF-36); postoperative pain scores; Visual Analog Scale (VAS) sleep scores; postoperative sufentanil consumption; need for rescue analgesia; length of Post-Anesthesia Care Unit (PACU) stay; length of hospital stay; and 90-day mortality. Safety outcomes will include assessments of hypotension, hypertension, bradycardia, tachycardia, arrhythmia, interventions for haemodynamic events, headache, dizziness, nausea, vomiting, local skin allergy, wound infection, and toxic reaction. Data will be analyzed following a modified intention-to-treat approach.

**Discussion:**

This study aims to provide high-quality evidence for the efficacy and safety of LP5 in preventing CPSP in patients undergoing knee arthroplasty.

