### 2.6 Safety outcomes

Safety outcomes will assess hypotension, hypertension, bradycardia, tachycardia, arrhythmia, interventions for hemodynamic events, headache, dizziness, nausea, vomiting, local skin allergy, wound infection, and toxic reactions.

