### 2.11 Sample size calculation

Based on previous studies, the standard deviation (SD) of the WOMAC Pain Scale prior to surgery is approximately 17, which corresponds to an 8–9 unit difference on the scale, representing the minimum clinically perceptible improvement (Wylde et al., 2015). To detect a 0.5 SD difference in WOMAC Pain Scale scores at 3 months postoperatively, with a two-sided α = 0.05 and 80% power, a sample size of 57 patients per group is necessary. Considering a potential dropout rate of 10%, we plan to enroll a total of 128 patients, with 64 patients in each group.

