### 2.12 Statistical analysis

The normality of continuous variables will be assessed via the Shapiro-Wilk test. Normally distributed data will be presented as mean (standard deviation), whereas non-normally distributed data will be presented as median (interquartile range). For normally distributed continuous variables, independent t-tests or repeated measures ANOVA will be utilized for analysis. For non-normally distributed variables, the Mann-Whitney U test or generalized estimating equations (GEE) will be employed. Categorical data will be expressed as numbers (percentages) and analyzed via the chi-square test or Fisher’s exact test, depending on the expected frequencies. The primary outcome, the WOMAC-pain score at 3 months postoperatively, will be analyzed via a linear regression model, adjusting for baseline variables including HADS scores, PCS scores, baseline WOMAC-pain scores, sex, age, and BMI. Additionally, interactions between the treatment group and baseline scores of HADS, PCS, and WOMAC-pain will also be examined. Covariates with *p*-values <0.10 will be retained in the final model. Secondary outcomes will undergo multiple testing corrections via the Benjamini–Hochberg method, with the false discovery rate (FDR) significance level set at q < 0.05. Odds ratios (OR) and 95% confidence intervals (CI) will be reported where applicable. To ensure the robustness of our primary findings, we will conduct a sensitivity analysis using the bootstrap method. The bootstrap analysis will involve 1,000 resamples to estimate the regression coefficients and their 95% confidence intervals (CIs). This analysis will provide additional validation for the stability of the initial regression results. All results will be analyzed using a modified intention-to-treat approach, including all patients who undergo randomization and for whom relevant data are available. Statistical analyses will be conducted via SPSS software (version 25.0; IBM SPSS). A two-sided *p*-value <0.05 will be considered statistically significant unless specified otherwise for false discovery rate (FDR) corrections. Missing data will not be imputed, and no interim analyses are planned.

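### The abstract's safety aim is stronger than 64 patients per group and a p<0.05 event comparison can support; harms should be reported as risk differences with intervals that work with empty arms

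*Protocol article*

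**What the plan says.** The Discussion paragraph of the abstract in the protocol article sets this aim: "This study aims to provide high-quality evidence for the efficacy and safety of LP5 in preventing CPSP in patients undergoing knee arthroplasty".

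Section 2.6 lists the outcomes that would carry the safety half: "Safety outcomes will assess hypotension, hypertension, bradycardia, tachycardia, arrhythmia, interventions for hemodynamic events, headache, dizziness, nausea, vomiting, local skin allergy, wound infection, and toxic reactions". All are naturally recorded as event or no event. No expected rate, relevant difference or margin is given for any of them.

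Section 2.12 covers event data with a general rule: "Categorical data will be expressed as numbers (percentages) and analyzed via the chi-square test or Fisher’s exact test, depending on the expected frequencies". The threshold is two-sided p<0.05. The false discovery rate correction is assigned to the secondary outcomes, which section 2.5 lists separately from the safety outcomes. Section 2.12 adds: "Odds ratios (OR) and 95% confidence intervals (CI) will be reported where applicable".

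The size of the trial is set in section 2.11 on the primary outcome only: "To detect a 0.5 SD difference in WOMAC Pain Scale scores at 3 months postoperatively", and after allowing for dropout, "we plan to enroll a total of 128 patients, with 64 patients in each group". The limitations in section 3 cover patch distance, length of follow-up and generalisability, but not precision for harms.

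**The concern.** A trial sized for a continuous pain score often has little power for binary harms. That is common and is not an error in itself. The difficulty is the pairing: the abstract sets safety beside efficacy as something the trial will give strong evidence on, while the stated analysis offers a test of difference and no bound on excess risk. For uncommon harms such a test will usually be non-significant whether or not LP5 causes them.

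The planned odds ratio interval would help, but it fails where it is most wanted. Wound infection, local skin allergy and toxic reaction are the events most specific to a patch worn beside a fresh incision, and they are the ones most likely to have an empty arm. The ordinary odds ratio and its interval are then zero, infinite or undefined. What is at stake is what the report can say about harms. The primary result and the conduct of the trial are not affected.

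**Working it through.** **Inputs from the article.** 64 per group and 1:1 allocation (sections 2.11 and 2.7); two-sided 0.05 and chi-square or Fisher (section 2.12).

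**Assumed inputs.** All event rates, because none are given; no dropout; Fisher used when an expected count is below 5, because section 2.12 gives no cut-off. With equal arms, that means fewer than 10 events in total at the rates used here.

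**1. The plan's own figure.** Section 2.11 states: "with a two-sided α = 0.05 and 80% power, a sample size of 57 patients per group is necessary". With n = 2(1.960 + 0.842)²/d² and d = 0.5, n = 15.70/0.25 = 62.8, so 63 per group (64 by the t-test). The figure of 57 comes back only with 9 units and SD 17: d = 9/17 = 0.529, n = 15.70/0.280 = 56.01, rounded up to 57. The dropout step is right: 57/0.9 = 63.3, so 64. The mismatch is a separate matter. What counts here is that no safety quantity enters the calculation.

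**2. Chance of missing a true harm.** Sum Bin(i; 64, p₁) × Bin(j; 64, p₂) over all 65 × 65 tables (i, j) with p ≥ 0.05.

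| Placebo → LP5 (assumed) | Missed |
|---|---|
| 1% → 5% | 94% |
| 2% → 6% | 93% |
| 2% → 10% | 64% |
| 5% → 10% | 84% |
| 5% → 15% | 53% |
| 5% → 20% | 24% |
| 10% → 20% | 65% |
| 10% → 30% | 17.5% |
| 20% → 30% | 74% |
| 20% → 40% | 29% |
| 25% → 50% | 15% |

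With 57 per group the miss rates are up to about 8 points higher.

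**3. Results that need no assumed rate.**
- Fisher, 5/64 against 0/64: p = 2 × (64·63·62·61·60)/(128·127·126·125·124) = 2 × 0.0288 = 0.058.
- Fisher, 6/64 against 0/64: multiply by 59/123, giving 0.028. Against an empty placebo arm, six events are therefore needed for significance.
- 0/64 in both arms: the Wilson upper limit for one arm is z²/(n + z²) = 3.84/67.84 = 5.7%. The Newcombe upper limit for the difference is √(5.7² + 0²) = 5.7 percentage points.
- 5/64 against 1/64: Fisher p = 0.21, Newcombe interval −1.8 to +15.5 points.

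**4. How often the odds ratio fails.** The chance that at least one arm is empty, with the same rate p in both arms, is 1 − [1 − (1 − p)⁶⁴]².
- p = 1%: 0.99⁶⁴ = 0.5256, so 1 − 0.4744² = 0.775.
- p = 2%: 0.98⁶⁴ = 0.2745, so 1 − 0.7255² = 0.474.

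**The case against.** The strongest reply is that the article states no safety hypothesis, so a missing margin contradicts nothing. The aims elsewhere (the abstract's Background, the Introduction and the close of section 3) concern efficacy or effectiveness, and the objectives listed in section 3 do not include safety. The praise of the evidence in the abstract can fairly refer to the randomised, double-blind, placebo-controlled design. The choice of effect measure and interval commonly sits in a SAP, which is not shown. Much of this stands, and it limits the point to an improvement. It does not remove the mismatch, because the abstract names safety as an aim and section 2.12 fixes a test.

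Three stronger readings are tempting, and the article does not support them.

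- *The significance test is the only safety provision.* It is not. Section 2.12 also gives counts, percentages and odds ratios with intervals where applicable, and that qualifier already allows for tables where the odds ratio cannot be computed. Section 2.10 sends serious adverse events to the Data Monitoring Committee within 24 hours. That oversight protects participants, although it yields no between-group estimate.
- *A non-significant result will be presented as proof of safety.* No section says so. It is an inference that a reader of the results could draw, and the plan does not block it.
- *The design misses most relevant harms, whatever they are.* The miss rate depends on rates the article does not give. Ten of the thirteen listed outcomes are haemodynamic or general symptoms (six and four), and nothing shows these to be rare. For commoner events a large increase is usually detected, as the 10% → 30% and 25% → 50% rows show.

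**Conclusion.** The point holds in a limited form. At 64 per group, a comparison judged at p<0.05 cannot support the safety half of the abstract's aim for uncommon harms, and the odds ratio interval does not reliably fill the gap. Under assumed rates, the chance of missing a moderate increase runs from about half (5% → 15%) to more than nine in ten (2% → 6%), while large increases in commoner events are usually found. The chance of an empty arm, and so of no usable ordinary odds ratio, is about 47% at a rate of 2% in both arms and about 77% at 1%. Only the results in step 3 of the working are free of assumed rates. This is a cheap improvement to reporting and wording; it leaves the primary analysis as it is.

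**What to change.** In section 2.12, add for the section 2.6 outcomes: *For each safety outcome, events per arm and the risk difference (LP5 minus placebo) will be reported with a 95% Newcombe or Miettinen-Nurminen interval. The upper limit will be given as the excess risk that the trial cannot rule out. A p-value above 0.05 will not be taken as evidence of safety.* Both intervals can be computed when an arm has no events.

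In the Discussion paragraph of the abstract, reword the aim as evidence on the efficacy of LP5 together with descriptive data on its safety.

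The cost is a few sentences, with no extra patients or data. The downside is a weaker safety claim.

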## 1 Introduction

As the population ages, the prevalence of knee osteoarthritis continues to rise, resulting in an increasing number of knee arthroplasty procedures (Nham et al., 2023). Although knee arthroplasty is a definitive treatment for this condition and offers significant benefits, chronic postsurgical pain (CPSP) remains a significant issue, affecting 10%–30% of patients undergoing the procedure (Beswick et al., 2012). CPSP not only diminishes the quality of life and surgical outcomes for patients but also escalates healthcare costs (Schug et al., 2019). Treating CPSP faces high failure rates, with systemic medications such as antidepressants and antiepileptics providing only limited efficacy and being associated with significant adverse effects (Steyaert and Lavand’homme, 2018).

The 5% lidocaine-medicated plaster (LP5) is a topical analgesic that provides pain relief and local anesthesia by inhibiting voltage-gated sodium channels in neurons (Baron et al., 2016). It has shown significant efficacy in treating postherpetic neuralgia and diabetic peripheral neuropathic pain (Pei-Lin et al., 2008; White et al., 2010). Research indicates that lidocaine in LP5 can penetrate the stratum corneum to reach peripheral nerve fiber endings, inhibiting the transmission of persistent nociceptive signals from peripheral nerves and reducing the sensitization and hyperexcitability of neurons in both the peripheral and central nervous systems (Maloney et al., 2021). Existing studies have shown that LP5 is an effective treatment for chronic localized neuropathic pain following knee surgery. Beginning on day 7 of use, 83% of patients (20/24) experienced a 50% reduction in dynamic mechanical allodynia within 3 months (Pickering et al., 2019). However, the effectiveness of LP5 in preventing CPSP following knee arthroplasty remains unclear. Most current research focuses on treating chronic pain, whereas our study emphasizes early intervention to prevent pain, particularly given the refractory nature of CPSP. This study aims to evaluate the efficacy of LP5 in preventing CPSP in patients undergoing knee arthroplasty. By thoroughly examining the impact of LP5 on CPSP, we aim to provide valuable insights and potentially establish a new standard for postoperative pain management, thereby improving patient outcomes.

## 2 Methods

This protocol adheres to the Standard Protocol Items: Recommendations for Interventional Trials (SPIRIT) guidelines, as detailed in Supplementary Material.

### 2.1 Study design and patients

This study is a dual-center, prospective, randomized, double-blind, placebo-controlled, parallel-group clinical trial. The trial will be conducted at the First Affiliated Hospital of Soochow University and Suzhou Xiangcheng People’s Hospital, enrolling a total of 128 patients. Recruitment is scheduled to take place from 16 July 2024 to 16 January 2025. The study flow diagram is shown in Figure 1.

**FIGURE 1 F1:**
[figure not shown]
Study flow diagram. LP5, 5% lidocaine-medicated plaster.

### 2.2 Inclusion criteria

Patients who meet the following criteria will be included.• Age ≥60 years;• American Society of Anesthesiologists (ASA) physical status I-III;• Body mass index (BMI) <35 kg/m^2^;• Scheduled for unilateral first knee replacement surgery;• Informed consent provided by patients and their families.

### 2.3 Exclusion criteria

The exclusion criteria include.• A known allergy to lidocaine or adhesives;• The presence of other severe chronic pain conditions;• Long-term opioid use;• A history of alcoholism;• Severe liver or kidney insufficiency;• A history of neurological or mental illness;• Severe visual, hearing, or speech impairments that prevent the completion of assessment.

### 2.4 Primary outcome

The primary outcome will be the Western Ontario and McMaster Universities Osteoarthritis Index (WOMAC) Pain Scale, assessed via telephone or in-person interviews at 3 months postoperatively. The WOMAC Pain score evaluates pain severity across five activities: walking, using stairs, sitting or lying down, standing upright, and being in bed. Responses range from “none” to “extreme,” which are then summed and transformed into a 0–50 scale (Bellamy et al., 1988).

### 2.5 Secondary outcomes

Secondary outcomes will include WOMAC stiffness, function, and total scales; Leeds Assessment of Neuropathic Symptoms and Signs (LANSS) Pain Scale; 36-Item Short Form Health Survey (SF-36); postoperative pain scores; Visual Analog Scale (VAS) sleep scores; postoperative sufentanil consumption; need for rescue analgesia; length of Post-Anesthesia Care Unit (PACU) stay; length of hospital stay; and 90-day mortality.

### 2.6 Safety outcomes

Safety outcomes will assess hypotension, hypertension, bradycardia, tachycardia, arrhythmia, interventions for hemodynamic events, headache, dizziness, nausea, vomiting, local skin allergy, wound infection, and toxic reactions.

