### 2.8 Study interventions

In this study, patients will apply an LP5 or placebo patch for 12 h daily on the day before surgery and on postoperative days 1, 2, and 3. The preoperative patch will cover the anticipated incision site, while the postoperative patches will be applied 1.5 cm from either side of the incision. The placebo group will apply a placebo patch, identical in appearance and packaging to the actual medication patch. The lidocaine patches and placebo patches used in this study will be manufactured by Beijing Tide Pharmaceutical Co., Ltd. To maintain blinding, both patients and researchers will remain unaware of group assignments. The patches will be applied by medical professionals who are not involved in patient recruitment or data collection. Randomization will be performed before the study begins by an independent researcher using a computer-generated table of random numbers. Group assignments will be sealed in opaque envelopes to maintain blinding of the investigators, patients, and data analysts, and these envelopes will only be opened after the study is completed. The schedule of patient enrolment, study interventions, and outcome assessments will follow the SPIRIT statement (Table 1). All surgeries will be performed by experienced surgeons who have conducted at least 300 knee arthroplasty procedures prior to the study.

**TABLE 1 T1:** Schedule of patient enrolment, study interventions and outcome assessment.

Time point	Study period								
	Enrolment	Allocation	Post-allocation					Close-out	Follow-up
	Pre-op visit	Pre-op 1 day	Intraoperatively	PACU	24 h post-op	48 h post-op	72 h post-op	Discharged	3 months
Patient enrolment									
Eligibility criteria	×								
Written informed consent	×								
Demographic data	×								
Baseline characteristics	×								
HADS	×								
PCS	×								
Randomization/allocation		×							
Study interventions									
5% Lidocaine Patch		×			×	×	×		
Placebo Patch		×			×	×	×		
Outcome assessment									
WOMAC-Pain Scale	×								×
WOMAC-Stiffness Scale	×								×
WOMAC-Function Scale	×								×
WOMAC-Total Scale	×								×
LANSS									×
SF-36									×
Post-op pain scores					×	×	×		
VAS Sleep score					×	×	×		
Post-op sufentanil use							×		
Need for rescue analgesia							×		
Length of PACU stay				×					
Length of hospital stay								×	
90-day mortality									×
Adverse Events									
Hypotension			×	×	×	×	×		
Hypertension			×	×	×	×	×		
Bradycardia			×	×	×	×	×		
Tachycardia			×	×	×	×	×		

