Arrhythmia			×	×	×	×	×		
HD Events Intervention			×	×	×	×	×		
Headache		×			×	×	×		
Dizziness		×			×	×	×		
Nausea and vomiting		×		×	×	×	×		
Local skin allergy		×			×	×	×		
Wound infection					×	×	×		
Toxic reaction		×			×	×	×		

According to SPIRIT, statement of defining standard protocol items for clinical trials.

HADS, hospital anxiety and depression scale; PCS, pain catastrophizing scale; WOMAC, Western Ontario and McMaster Universities Osteoarthritis Index; LANSS, leeds assessment of neuropathic symptoms and signs; SF-36, Short Form Health Survey; Pre-op, Preoperative; Post-op, Postoperative; VAS, visual analogue scale; PACU, post-anaesthesia care unit; HD, haemodynamic; h, hours; SPIRIT, Standard Protocol Items: Recommendations for Interventional Trials.

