### 2.9 Anaesthetic care

Intraoperative monitoring will include non-invasive blood pressure (NIBP), electrocardiography (ECG), pulse oximetry (SpO_2_), radial artery blood pressure, and nasopharyngeal temperature. Anesthesia will be induced with an intravenous injection of propofol at 1.5–2.5 mg/kg, combined with sufentanil at 0.2–0.4 μg/kg for analgesia. This will be followed by an intravenous injection of rocuronium at 0.6–0.9 mg/kg to achieve muscle relaxation. After induction, an endotracheal tube will be inserted, and its placement will be confirmed. The patients will receive mechanical ventilation, maintaining end-tidal carbon dioxide between 35 and 45 mmHg. Hypotension (mean arterial pressure <65 mmHg or a decrease of 20% from baseline) and bradycardia (heart rate <50 beats/min) will be treated as needed. A thermal blanket will be used during the operation to maintain nasopharyngeal temperature above 36°C. Additional doses of rocuronium will be administered as necessary to maintain muscle relaxation throughout the procedure. Continuous monitoring will include ECG, NIBP, SpO_2_, and bispectral index (BIS), with BIS values maintained between 40 and 60. Both groups of patients received 50 mg of flurbiprofen axetil during surgery. Postoperatively, all patients were transferred to the PACU. During their stay in the PACU and hospitalization, if a patient reported pain with an NRS score of 4 or higher, 5 μg of sufentanil was administered for analgesia, and the total dosage was recorded.

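### Table 1 schedules no haemodynamic assessment on the pre-operative patch day, so non-serious haemodynamic events on the first exposure are not collected

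*Protocol article*

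**What the plan says.** Section 2.6 names the haemodynamic safety outcomes once and gives no time window: "Safety outcomes will assess hypotension, hypertension, bradycardia, tachycardia, arrhythmia, interventions for hemodynamic events".

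Section 2.8 sets the exposure: "an LP5 or placebo patch for 12 h daily on the day before surgery and on postoperative days 1, 2, and 3". No patch is scheduled on the day of surgery itself.

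Table 1 (section 2.8) sets the assessment times. Its columns run "Pre-op visit Pre-op 1 day Intraoperatively PACU 24 h post-op 48 h post-op 72 h post-op Discharged 3 months". The patch rows, such as "5% Lidocaine Patch", are marked at Pre-op 1 day and at 24, 48 and 72 h. The six haemodynamic rows, of which the last is "HD Events Intervention", are marked intraoperatively, in PACU and at 24, 48 and 72 h. The row "Toxic reaction" carries the same marks as the patch rows.

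Section 2.10 requires serious adverse events to be reported immediately, related or not. It is not tied to a visit, and its own example is lasting haemodynamic instability. Section 2.12 gives chi-square or Fisher's exact tests for categorical data. It does not say whether safety events are combined across time points.

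**The concern.** The haemodynamic rows do not line up with exposure. They include two periods with no patch scheduled and omit one day on which a patch is worn. The omitted day is the first exposure, and the only one not preceded by anaesthesia and surgery and accompanied by postoperative opioid. A change in blood pressure or heart rate that day would be the easiest to attribute to the patch.

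The blank does not look deliberate. Five other adverse-event rows are marked on that day, so adverse events are already being recorded, and no reason is given for leaving out the cardiovascular ones. The abstract presents the trial as a source of evidence on safety as well as efficacy. For cardiovascular safety, that evidence would lack part of one exposure day in four.

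**Working it through.** No figure in the article bears on this point, so the check is a reading of Table 1 against the patch schedule in section 2.8.

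| Table 1 row | Pre-op 1 day | Intraop. | PACU | 24 h | 48 h | 72 h |
|---|---|---|---|---|---|---|
| Patch (LP5 or placebo) | × | – | – | × | × | × |
| Six haemodynamic rows | – | × | × | × | × | × |
| Toxic reaction, skin allergy, headache, dizziness | × | – | – | × | × | × |
| Nausea and vomiting | × | – | × | × | × | × |
| Wound infection | – | – | – | × | × | × |

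**Step 1: coverage of exposure.** There are four patch time points. Three (24, 48, 72 h) have a haemodynamic assessment and one (Pre-op 1 day) does not: 1/4 = 25% of patch days uncovered.

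**Step 2: assessments without a patch.** There are five haemodynamic time points. Two (intraoperative, PACU) have no patch scheduled and three do.

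**Step 3: is there a common rule behind the blank?** Four adverse-event rows copy the patch rows exactly, and nausea and vomiting adds only PACU. Wound infection is blank before surgery for the obvious reason that there is no wound. The six haemodynamic rows are the only ones left blank on a patch day when the event could occur.

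**Step 4: what is still captured that day?** Symptoms, skin reactions and anything recorded as a toxic reaction are scheduled. Serious events are reportable under section 2.10. What remains uncollected is non-serious haemodynamic events.

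**Step 5: why the windows should be shown apart.** Suppose, which the article does not state, that each event were analysed as ever/never over all columns. Let *b* be the intraoperative/PACU risk, assumed equal in both arms and independent of patch-day events, and let *p* be the patch-day risk. The pooled risk in an arm is 1 − (1 − *p*)(1 − *b*) = *b* + (1 − *b*)*p*. The difference between arms is then

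(1 − *b*) × (*p* on LP5 − *p* on placebo).

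The patch effect shrinks by the factor (1 − *b*). No value of *b* is given. For assumed values of 10%, 30%, 50% and 70% the factor is 0.9, 0.7, 0.5 and 0.3. These show the direction and form of the dilution and are not estimates for this trial.

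**The case against.** The strongest reply is that little is missing. All six rows are marked at 24, 48 and 72 h, the columns of the three postoperative patches. A reader who noticed only the intraoperative and PACU marks might infer that haemodynamic effects are looked for only when no patch is worn. Table 1 does not support that.

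Nor is the first exposure missed altogether, for the reasons in step 4 of the working.

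A reader might also infer that the haemodynamic comparison will be swamped by anaesthetic events. That needs two things the article does not supply: pooling across windows, and event rates. Section 2.12 states no pooling, Table 1 collects by time point, and the handling of windows may sit in the statistical plan that section 2.10 mentions. The criterion in section 2.9, "Hypotension (mean arterial pressure <65 mmHg or a decrease of 20% from baseline", says when hypotension is treated under anaesthesia. It is not stated to be the adverse-event definition, so it does not show how many events will be counted. Even with pooling, a blinded randomised comparison would suffer dilution rather than bias between arms under the assumptions in step 5.

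Finally, intraoperative and PACU recording is worth having: surgery follows the first patch by a day, and these windows can show carry-over.

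All of this stands, and it limits the size of the point. None of it fills the six blank cells.

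**Conclusion.** The point holds in a narrow form. As written, Table 1 leaves non-serious haemodynamic events unscheduled on the pre-operative patch day, one of four patch days and the only one before anaesthesia and surgery, while five other adverse-event rows are recorded then. This rests only on reading Table 1 against section 2.8.

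Showing the windows separately is a sensible addition but corrects no stated rule. The dilution argument is conditional on pooling and on an unknown background rate, so no power figure belongs with it. Severity is minor: the primary outcome, the sample size and the treatment comparison are unaffected.

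**What to change.** 1. In Table 1, mark the six haemodynamic rows in the Pre-op 1 day column and add the matching line to the case report form. This assumes that vital signs are taken while the patch is applied or worn that day, which the article does not describe and the sponsor should confirm.
2. In the safety table, show haemodynamic events in two windows: patch days (the pre-operative day and postoperative days 1 to 3), and the intraoperative/PACU period. Keep the second window, because it remains informative.

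The cost is one more recording per patient and one more split in the table, with fewer events in each part. No additional patients and no change to treatment are needed. Apart from the new pre-operative mark, the split uses data already scheduled by time point.
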